## Abstract

**Background:**

The COVID-19 pandemic has had disproportionate economic and health impacts on self-employed workers in Nigeria, particularly self-employed women and youth. Though uniquely different, the COVID-19 pandemic shares similarities with events such as childbirth, family, and health emergencies. Self-employed young women lack adequate support structures to cope with disruptive life events, which have negative consequences for their well-being. This is concerning, as 86% of women in the Nigerian labor force are self-employed.

**Objective:**

The project’s first objective is to conduct a gendered situational analysis to address the question of how the COVID-19 pandemic and other life events affect the paid and unpaid work and the physical, mental, and social well-being of self-employed young women in Nigeria; their strategies for coping with such events; and how their experiences compare with those of self-employed young men. Informed by this analysis, the second objective is to coproduce and pilot-test a gender-transformative intervention that integrates social protection and promotes well-being.

**Methods:**

This multimethod project has 3 components. The first is a situational analysis of the impact of the pandemic and other significant life events on the work and well-being of self-employed young women vis-à-vis self-employed young men. This involves qualitative interviews with approximately 60 self-employed young women and men and a digital storytelling initiative to represent some of these stories in video format. Secondary data analysis of the Nigerian General Household Survey and the COVID-19 Longitudinal Phone Survey will be conducted. Furthermore, a scoping review of the impact of significant life events, including the COVID-19 pandemic, on self-employed workers in low- and middle-income countries will be conducted. The second component is the coproduction of interventions involving qualitative interviews with self-employed young women, members of their support network, and policy makers to find out their views on how to support self-employed women. It also entails an analysis of policies relevant to self-employed women in Nigeria and theory of change workshops to create a map for achieving the long-term goal of improving their resilience. Furthermore, a systematic review of interventions to improve the job quality and well-being of self-employed workers will be conducted. The third component is a pilot of the coproduced interventions in a quasi-experimental study involving 300 participants to assess feasibility, acceptability, cost, and potential effectiveness.

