#### Aim 3: Pilot Trial of the Intervention Packages

##### Overview

The aim of this phase of the project is to pilot the coproduced intervention packages developed in phase 2 of the project to assess their feasibility, acceptability, cost, and potential effectiveness. This phase will also assess the factors that facilitated and hindered the implementation of the piloted intervention packages and what needs to be learned before scaling up.

The pilot of the ARISE&WIN interventions has been planned as a quasi-experimental study with a prepost design. The design was chosen because there was unanimity around it being feasible while allowing us to draw conclusions about the potential effectiveness of various interventions. The study will consist of 3 arms. One of the intervention groups will receive the capacity building intervention package. The second intervention group will receive the social protection intervention package in addition to the capacity building intervention package. The capacity building and the social protection interventions will be finalized during the coproduction process. The third group will be a control group serving as a comparison group, and participants will not receive any intervention. The pilot will be conducted in the LGAs of Greater Ibadan, where situational analysis has been conducted. The LGAs will be stratified into urban, periurban, and rural LGAs and randomly assigned to 1 of the 2 intervention groups or the control group. On the basis of recommendations from literature [43,44] on pilot trials, a sample size of 120 participants would be large enough to assess feasibility and other outcomes of interest in the pilot study. To account for possible attrition, the sample size would be rounded up to 150 in total, with 50 participants per arm of the trial. Frequency matching will be conducted to ensure that across the intervention and control LGAs, the participants will have similar characteristics based on age and their sector of occupation. Participants will be recruited through advertisements on social media platforms where self-employed young women are active. Announcements will also be made at business association meetings to identify eligible participants. Participants will also be recruited through partner organizations (SMEDAN and the Centre for Support of Women in Unpaid and Informal Employment in Nigeria) that work with self-employed young women.

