##### Feasibility

The feasibility of recruitment will be measured by the percentage of the sample size that is recruited. To measure the retention rate of participants, the attendance of the participants in the intervention training sessions and their level of compliance with intervention guidelines will be recorded. Furthermore, facilitators and participants in the intervention will be asked questions about the feasibility of scaling the intervention and conducting a similar but larger-scale trial in both the survey questionnaires and in-depth interviews that will be administered at the end of intervention delivery.

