##### Analysis

Participants’ background characteristics will be summarized using frequencies and percentages for categorical variables, such as education, religion, marital status, etc. Means and SDs will be computed for numerical variables, such as age and income. The comparison of study outcomes across the 3 groups will be done using chi-square tests and 1-way ANOVA, as appropriate, at *P*<.05. Pairwise comparisons will also be done to compare the 2 intervention groups with the control group. Bonferroni adjustment will be made to correct for error rates that may be introduced by multiple comparisons. If necessary, generalized linear models will be fitted to adjust for confounders and pertinent variables that exhibit baseline differences between the study groups (eg, education status). Descriptive statistics and multivariate regressions will be adopted to analyze the Likert-scale questions in the survey on the feasibility and acceptability of the interventions to the participants and facilitators. All qualitative data in the study will be analyzed using the reflexive thematic analysis method.

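### The Abstract gives the pilot 300 participants, the Methods derive 150, and the recruitment-feasibility percentage depends on which is meant

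*Protocol article*

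**What the plan says.** The protocol article gives the size of the pilot in two places.

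- Abstract, Methods paragraph: "The third component is a pilot of the coproduced interventions in a quasi-experimental study involving 300 participants".
- Methods, Aim 3: Pilot Trial of the Intervention Packages, Overview: "a sample size of 120 participants would be large enough to assess feasibility and other outcomes of interest in the pilot study". The text then adds an allowance, introduced by "To account for possible attrition", and concludes that "the sample size would be rounded up to 150 in total, with 50 participants per arm of the trial". The same section fixes the number of groups: "The study will consist of 3 arms".

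The planned number is then used in the Feasibility section of Aim 3: "The feasibility of recruitment will be measured by the percentage of the sample size that is recruited". No figure is repeated there.

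The figure of 300 does not occur again. The Results section and its status table give dates for the pilot but no planned or achieved number of participants.

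**The concern.** Both statements are in force. Neither comes from an amendment log, and both describe the Aim 3 pilot with the same purposes. An article may leave detail to a fuller protocol, but here it gives two values for one quantity.

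The planned sample size is the denominator of the recruitment measure, and feasibility is the first purpose named for the pilot. With two denominators in print, the same recruitment count yields two percentages that differ twofold. The Results section says recruitment was to close in January 2025 and that the packages are already being delivered. Unless the target is settled in writing before the result is reported, the denominator could be chosen with the count already known. The Discussion says the pilot results will be used to prepare a large-scale efficacy trial, so a recruitment rate taken against the wrong target could carry into its planning. Many readers will also see only the Abstract.

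**Working it through.** **Inputs from the article**

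- Planned total, Abstract: 300.
- Number judged sufficient, Aim 3 Overview: 120.
- Planned total after the attrition allowance, Aim 3 Overview: 150, as 50 in each of 3 arms.
- Attrition rate: not stated.
- Recruitment measure, Feasibility section: number recruited / planned sample size.
- Significance level, Analysis section: .05, with Bonferroni adjustment. Sidedness and the number of comparisons are not stated. I assume two-sided tests and two comparisons with control.

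**Step 1. Reproduce the Methods figure.** 3 x 50 = 150. The implied attrition is 1 - 120/150 = 0.20, and 120/(1 - 0.20) = 150. (Multiplying up instead, 120 x 1.25 = 150.) The Methods figure is internally consistent.

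**Step 2. Try to reach the Abstract figure from the same inputs.** 300/3 = 100 per arm, against 50 stated. From 120, the attrition needed is 1 - 120/300 = 0.60. Neither 100 per arm nor 60% attrition appears anywhere. 300/150 = 2.

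**Step 3. Effect on the recruitment measure.**

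| Recruited | Against 150 | Against 300 |
|---|---|---|
| 120 | 80% | 40% |
| 150 | 100% | 50% |
| 300 | 200% | 100% |

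**Step 4. Effect on precision, as illustration only.** Participants are treated as independent, with no loss to follow-up.

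- 95% half-width for a proportion of 0.80 (an assumed value), 1.96 x sqrt(0.80 x 0.20/n): 6.4 percentage points at n = 150 and 4.5 at n = 300.
- 95% half-width for a difference in means between two arms, in SD units, 1.96 x sqrt(2/n): 0.39 at 50 per arm and 0.28 at 100 per arm.
- The same at a two-sided level of .05/2 = .025: 0.45 and 0.32.

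Doubling n halves the variance, so widths change by sqrt(2) = 1.41, not by 2.

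The Aim 3 Overview assigns whole local government areas (LGAs) to arms, so independence does not describe this design. If the number of LGAs is unchanged and m participants per LGA become 2m, then with within-LGA correlation r the ratio of widths is sqrt{2[1 + (m - 1)r]/[1 + (2m - 1)r]}. This is below 1.41 for any r > 0. The figure of about 1.4 is therefore an upper limit in that case.

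**Step 5. Could 300 count other people?** The Outcomes section adds questions for members of the women's support networks, and the Aim 3 Overview adds a survey of facilitators. Neither gives a number or says that these people belong to the pilot sample. The support-network questions are tied to women who take part in the intervention. If one member were counted for each woman in the two intervention arms (my assumption), the total would be 150 + 100 = 250, not 300.

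**The case against.** The best reply is that a careful reader can tell which number is meant. Only 150 has a derivation and an arm split. The Feasibility section belongs to the same Aim 3 Methods as that derivation, so the sample size it refers to is most naturally 150. The 300 stands alone in one Abstract sentence and may simply be a slip or a leftover. This stands as far as it goes, and for that reason the recruitment denominator should not be called undefined. It does not close the point. The article nowhere confirms 150 against the Abstract, gives no recruited count, and leaves the Abstract reader with a number twice as large.

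A reader might also infer three stronger things that the document does not support.

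- **That the same recruitment would count as success or as failure.** The Feasibility section defines a percentage and sets no threshold, so neither 100% nor 50% carries a label.
- **That the conflict hides the intended precision.** No power, precision or detectable difference is stated for either number. The size rests on recommendations for pilot trials.
- **That precision differs by a factor of two.** The factor of two applies to the sample size, the recruitment denominator and, under independence, the variance. Interval width changes by about 1.4 at most under the conditions in step 4.

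Finally, a wider count that includes support-network members or facilitators might lie behind 300. The text gives no numbers to support this, but the authors should be asked.

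**Conclusion.** Wrong as written. The Abstract and the Methods give two planned sizes for one pilot, 300 and 150, and nothing in the article reconciles them. The calculation in the Methods is sound. The fault is the inconsistency between the two sections, not an error of arithmetic.

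The consequence that matters is for the recruitment measure, which differs twofold for any count. That result needs no assumption beyond the definition in the Feasibility section. The precision figures are secondary. They rest on independent participants, no loss to follow-up, an assumed proportion of 0.80, two-sided tests and two comparisons with control. They should not be read as the trial's actual sensitivity.

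The document favours 150 but does not establish that 150 is the number being recruited.

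**What to change.** Confirm the operative target and state it identically in the Abstract and the Aim 3 Overview.

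- If it is 150, change the Abstract from 300 to 150.
- If 300 was actually planned, give its real basis and the split per arm in the Aim 3 Overview, and say who is counted (enrolled women only, or also support-network members or facilitators). A justification should not be worked backwards from 300: the present text calls 120 sufficient and offers no support for a larger evaluable number.

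In either case, name the chosen number under Feasibility as the denominator of the recruitment percentage, and do so before that percentage is reported.

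The cost is a correction to the text. Nothing in the conduct of the pilot changes if the number actually being recruited is the one kept.

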**Results:**

This project was funded in October 2022. Data collection for the project commenced in May 2023 and will end in November 2025. Data collection for the situational analysis and coproduction of intervention phases have been completed while the pilot of intervention packages is underway.

**Conclusions:**

This project will advance knowledge of the impact of the COVID-19 pandemic and other significant disruptive life events on the work and well-being of self-employed young Nigerian women and provide coproduced solutions to mitigate their effects.

**International Registered Report Identifier (IRRID):**

DERR1-10.2196/69577

## Introduction

### Background

The COVID-19 pandemic has had disproportionate economic and health impacts on self-employed workers. In high-income countries, self-employed workers lost more earnings and jobs than employees [1,2]. In low- and middle-income countries (LMIC), the economic consequences of the pandemic were even greater. With little to no social protection, paid sick leave, savings, or access to credit, many self-employed workers in LMIC continued to go out to work at the height of the pandemic, exposing them to an increased risk of infection [3]. They also faced adverse mental health consequences, including fear of infection and income-related anxieties [4,5].

According to the International Labour Organization, self-employed persons are workers whose remuneration directly depends on the profit from the goods and services they produce. They include employers, own-account workers, members of producers’ cooperatives, and contributing family workers [6]. Self-employment accounts for 70% of employment globally [7]. LMIC generally have a higher proportion of self-employed workers in their labor force [8]. In Nigeria, 80% of workers and 86% of women in the labor force are self-employed, making it an apt setting to examine the impacts of the COVID-19 pandemic on self-employed workers [9,10]. Self-employed workers in Nigeria usually work in agriculture, wholesale and retail trade, catering and food services, fashion design, machinery repair, the digital economy, etc. Many self-employed workers operate in the informal economy, where economic activities are unregulated by the government and other formal institutions of society [11].

Self-employed women face certain disadvantages in the labor market. They have fewer employees and lower earnings and profits [12-15]. A report from the Organisation for Economic Co-operation and Development [16] suggested that compared to self-employed men, self-employed women earn less and have smaller businesses because they have less access to capital, enter into less competitive sectors, and are more likely to operate in the informal economy. The COVID-19 pandemic heightened these disadvantages. United Nations Women [17] reported that 25% of self-employed women lost their jobs during the pandemic compared to 21% of self-employed men. Furthermore, the US Global Leadership Coalition revealed that in every region of the world, female-owned businesses experienced higher closure rates during the first year of the pandemic compared to male-owned businesses [18]. In Nigeria, about 44% of women-led businesses closed during the pandemic compared to 33% of men-led businesses [19].

Data from Ibadan in the southwestern part of Nigeria collected in 2021 revealed the pandemic’s heightened impacts on self-employed women [20]. The data came from 29 semistructured interviews and 504 questionnaires administered to self-employed young men and women from diverse sociodemographic backgrounds working in various sectors. Many self-employed workers experienced financial hardship, resulting in distress. The lockdown prevented 38.8% of self-employed young women from doing business-related tasks and forced 23.6% of women (vs 17.8% of men) to run their businesses from home. Fewer women than men (32.5% vs 40.6%) continued going out to work during lockdowns. During the pandemic, 65.8% of women reported facing “much” or “a lot” of financial hardships. Among self-employed youth who had started their businesses before the COVID-19 pandemic, 3.5% of 255 women (vs 7.6% of 197 men) were able to start a new revenue stream to cope with the effects of the pandemic, and only 1 woman received government monetary assistance.

Though uniquely unexpected and disruptive, the COVID-19 pandemic has similarities with other disrupters of paid work, such as childbirth, family, and health emergencies. Such events especially affect women, who are seen as traditional caregivers and perceived to have more time flexibility. This leads to greater economic losses compared to men, leaving women more vulnerable, further perpetuating gender inequities. Many women lack adequate support to deal with such events. Thus, building supportive structures for self-employed young women is an urgent imperative.

In Nigeria, there are ongoing programs sponsored by the government and other financial institutions targeted at women in business. An example is the *Women in Self-employment Program* domiciled in the Small and Medium Enterprises Development Agency of Nigeria (SMEDAN), which provides self-employed women with financial assistance, business training, mentorship, and access to markets [21]. Another example is the *Womenpreneur Pitch-a-ton* organized by Access Bank, which offers mini Master of Business Administration scholarships to beneficiaries alongside grants [22]. There have been testimonials on the positive effects of these programs, but the evidence for these remains anecdotal. The impact of these programs is not evaluated in the systematic way that trials are done, thus limiting the examination of their effectiveness and generalizability. In addition, the development and implementation of most of these programs lack the vital element of coproduction, thus limiting impact. Coproduction [23] is a collaborative, participatory approach where those who will ultimately benefit or be impacted by research or an intervention initiative are a part of its development process; research or the intervention development and implementation is conducted with them rather than on them. Participatory approaches are more likely to result in research or interventions that are shaped by the needs, values, and goals of the stakeholders, thereby increasing the uptake of the output. Beyond these instrumental gains, coproduction with those with lived experience is also an ethical and rights-based imperative. In sum, our Advancing Resiliency in Self-Employed Young Women in Nigeria (ARISE&WIN) study seeks to bridge these gaps in the lack of in-depth knowledge about the lives, stressors, and coping strategies of young self-employed women and the lack of coproduced and well-evaluated interventions to support their resilience and well-being.

### Research Aims

The project’s first aim is to conduct a gendered situational analysis of how the COVID-19 pandemic and other significant life events (childbirth, family, and health emergencies, etc) affect the paid and unpaid work and mental, physical, and social well-being of self-employed young women in Nigeria; their strategies for coping with such events; and how their experiences compare with those of self-employed young men. To achieve this aim, the project has the following objectives:

Explore through qualitative interviews, digital storytelling, and a scoping review self-employed young women’s and men’s experiences of the COVID-19 pandemic and life events that impact work and well-beingQuantitatively examine the gender-differentiated impact of the pandemic on the work and well-being of self-employed young people in Nigeria using longitudinal secondary data

The project’s second aim is to coproduce nationally scalable intervention packages in order to support self-employed young women in Nigeria to cope better with disruptions to their work and promote their well-being. The specific objectives under this aim are as follows:

Synthesize existing evidence on interventions for social protection, job quality, and well-being promotion for self-employed youth using a systematic review, policy analysis, as well as qualitative interviews with self-employed young women, members of their support network, and policy makersCoproduce, using theory of change and co-design workshops, intervention packages to improve the resilience of self-employed young women in Nigeria against significant life events

The third aim of the project is to pilot and assess the feasibility, acceptability, cost, and potential effectiveness of the coproduced intervention packages on the resilience, job quality, and mental and physical well-being of self-employed young women, using a quasi-experimental study. The study focuses on young women aged between 15 and 35 years [24].

## Methods

### Study Setting

The project is being conducted in Oyo State in southwest Nigeria. Oyo State is a suitable site to capture a wide range of self-employed young workers’ experiences, given its large and diverse population, with migrants from across Nigeria, and the baseline data that the research team has from here. The study is being conducted in urban, periurban, and rural local government areas (LGAs) of Ibadan, the capital of Oyo State, because of the proximity to certain facilities of the Oyo State Government that will be used in the pilot of the coproduced intervention packages. Ibadan is the third most populous city in Nigeria and has about 4 million inhabitants [25]. The main economic activities carried out by the inhabitants are agriculture, trade, public service employment, handicrafts, and factory work [26]. Ibadan is a highly commercial city, with the presence of markets and businesses all over the metropolitan area. Many young people in the state are engaged in self-employment across sectors, such as garment making, shoemaking, hairdressing, building construction, catering, and food vending. They also work as graphic designers, printers, electricians, auto mechanics, etc.

